## Study design and management

RASTA will be a multicenter, randomized, parallel-arm, open labeled, superiority trial.

The trial will be conducted in five Italian Institutions with proven experience in pancreatic surgery and an established ERAS program.

THE RASTA trial will be managed and coordinated by the School of Medicine and Surgery of the Milano-Bicocca University and the HPB Unit of the IRCCS San Gerardo Hospital, Monza, Italy. The coordinating center will also be responsible for treatment allocation and monitoring, and statistical analysis with the support of the Centre of Biostatistics for Clinical Epidemiology of the Milano-Bicocca University.

The trial has been registered at ClinicalTrials.gov (ID: NCT04438447; date: June 16, 2020) and approved by the Italian Drug Agency (AIFA; number: EudraCT 2020–005483-66; date: September 13, 2021).

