### Screening and randomization processes

After being screened for inclusion and exclusion criteria, patients or their legal representative will be asked to sign a written informed consent. After enrolment in the study, patients will be randomly allocated into two arms. All reasons for exclusion after screening will be recorded.

Patients will be randomly allocated to ERAS or ERAS plus PN at 8:00 PM of the day of surgery, or at 8 AM in the morning of postoperative day one if the operation was concluded after 8 PM. Randomization will be performed by a computed-generated permuted-block sequence. A specific code will be generated for each center to achieve equivalent grouping. The allocation ratio will be 1:1 with a block size of 4. Randomization will be stratified by neoadjuvant chemo- or chemoradiation therapy and center. Randomization will be competitive among centers.

Surgeons and patients will not be blinded to treatment arm. Masking to allocation will be impossible to achieve for the study nature and design.

Patient chart evaluation and data entry for outcome recording will be done by trained assessors (selected in each center) and not directly involved in patient care and thus masked to patient allocation. Clear information on patient allocation will not be released to any hospital personnel with exception of ethical committee members under specific request.

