#### H1 hypothesis

The administration of a parenteral nutrition added to the ERAS protocol will positively affect the CCI as compared to standard of care (ERAS).

Secondary outcome measures will be:

- Actual daily calories delivered by PN.- Rate of unplanned artificial nutrition (for control group).- Rate and severity of complications at 90 days after discharge.- Rate of surgical site infections (16)- The rate and severity of postoperative pancreatic fistula (17)- Rate and severity of DGE (18)- Rate and severity of hemorrhage (19)- Length of stay (LOS) based on predefined criteria- Actual LOS- Rate of reoperation.- Rate and duration of intensive care treatment.- Rate of hyperglycemia (blood glucose >180 mg/dl)- Use of insulin (subcutaneous bolus or continuous infusion)- Δ plasma prealbumin levels (baseline, postoperative day 1 and 6)- Use of morphine- Readmission rate- Body weight (90 days)- 90-day mortality

Any attending surgeon will decide the day of discharge according to his individual clinical judgement. However, LOS will be also calculated by the achievement of pre-specified discharge criteria (full patient mobilization, pain controlled by oral therapy, full tolerance to oral feeding). In particular, a visual analog pain scale ≤2 must be achieved for safety discharge.

Post-discharge follow-up will be accomplished by weekly outpatient visits. Also telephone interviews will be allowed to monitor patient health state, but in case of warning signs or symptoms of a complication, patients will be asked to refer to the hospital where the operation was performed for further clinical evaluation.

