## Statistical planning

The sample size of 120 patients per group is necessary to provide an 80% power to detect at least a 30% reduction in the CCI, which is expected to be around 23 (median) (IQR 21–31) or mean 27 (±20 SD) in complicated patients of the control group. The hypothesized reduction of 30% is based on sound clinical relevance meaning that such reduction will have a consistent and significant impact of the postoperative course with advantages on well-being, quality of life, shorter length of hospitalization and a relevant reduction of heath care burden and resources. The median CCI of 23 is retrieved from a previous publication (20). The rate of complication in this type of surgery is expected to be approximately of 60%.

A Mann–Whitney test is considered, type I error rate is fixed at 5% (two tails) and an expected drop-out of 10% is taken into account.

For the binary end-points, the relative risk (RR) with the corresponding 95% confidence interval, comparing the two groups, will be estimated. For the primary end-point, also the risk difference (RD) will be computed. For the numerical end-points the difference in the location parameter (i.e., median pairwise difference) between the two groups with the corresponding 95% confidence interval will be computed. Fisher test and Mann–Whitney test will be adopted to evaluate univariate associations. Incidence of complications over time in the two groups will be described according to the Nelson-Aalen cumulative hazard estimator also accounting for multiple events per patient. The incidence in the two groups will also be compared by computing the incidence rate ratio (with 95% confidence interval). This analysis will be performed both considering all complications and only major complications.

A multivariate quantile regression model (focused on median, 25^th^ and 75^th^ percentiles) will be used to identify factors associated with the primary endpoint and to evaluate the effect of treatment adjusting for possible residual confounding. Logistic regression will also be used to model the probability of CCI >23. Using these regression models, the effect of PN over controls on the CCI will be also investigated within pre-specified subgroups to account for possible effect modification. The pre-specified risk factors for this analysis will be:

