- Nutritional risk screeing-2002 (≥3)- Body mass index (> 30)- Sex (male)- Age (>70 years)- Charlson comorbidity index (>4)- ASA score (=3)- Blood loss (≥500 mL)- Duration of surgery (>360 min)- Biliary stenting- Diabetes- Pylorus-preserving PD (vs. Whipple)- Pancreatic ductal carcinoma (vs. others)- Fistula risk score (≥7)- ERAS overall compliance (>70%)

All analyses will be done based on the principles of “intention-to-treat” and “per-protocol” and performed with the R software.

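### The primary CCI test ignores the randomisation strata, and 90-day weight is compared without its baseline: the analyses stay valid but give up precision that costs almost nothing to keep

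*Protocol article*

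**What the plan says.** **Randomisation.** Under *Screening and randomization processes*: "Randomization will be stratified by neoadjuvant chemo- or chemoradiation therapy and center", and "The allocation ratio will be 1:1 with a block size of 4". *Study design and management* gives the number of centres: "The trial will be conducted in five Italian Institutions with proven experience in pancreatic surgery and an established ERAS program". Five centres by two neoadjuvant categories make up to 10 strata.

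**Primary comparison.** *Statistical planning* sizes the trial on an unstratified rank test: "A Mann–Whitney test is considered, type I error rate is fixed at 5% (two tails". For numerical endpoints the effect measure is the median pairwise difference between arms, with no adjustment mentioned. For testing: "Fisher test and Mann–Whitney test will be adopted to evaluate univariate associations".

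**Models.** The same section adds a quantile regression, partly to adjust the treatment effect for residual confounding, and a logistic model for CCI above 23. The list of 14 factors that follows includes neither centre nor neoadjuvant therapy. Neoadjuvant treatment is recorded (*Case report form*).

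**Weight.** The secondary outcomes, under *H1 hypothesis*, include "Body weight (90 days", with no mention of change or baseline. Prealbumin, in the same list, is defined as a change. Weight is measured before randomisation, at discharge and at three months (Table 2).

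**The concern.** Blocking within strata forces the arms to be nearly balanced on centre and neoadjuvant status. That removes the between-stratum part of the outcome variance from the treatment comparison. A test that ignores the strata still counts that part as noise, so its standard error is too large whenever the strata are prognostic.

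Centre effects are plausible from the article itself. Operative technique follows each centre's own standards (*Procedures common to both arms*), and outcome assessors are nominated per centre and trained by that centre's principal investigator (*Pre-trial training*). The sponsor also chose these two factors for stratification, yet they are absent from the factors named for the models.

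For weight the reasoning is simpler. Adults differ widely in body weight before surgery, so a comparison of unadjusted 90-day weights is dominated by body size rather than by what happened after surgery.

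At stake is precision, and agreement between design and analysis. It is also better to settle adjusted versus unadjusted in advance than once results are known.

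**Working it through.** **1. The plan's own figure.** Inputs from *Statistical planning*: control mean 27, SD 20, 30% reduction (27 × 0.30 = 8.1 points), two-sided 5%, 80% power, and "an expected drop-out of 10% is taken into account".

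n per arm = 2 × (1.960 + 0.842)² × 20² / 8.1² = 96 for a comparison of means. Allowing for the rank test and drop-out:
- 96 × π/3 → 101; 101 / 0.9 → 113
- 96 × 1.15 → 111; 111 × 1.1 → 123
- 96 / 0.864 → 112; 112 / 0.9 → 125

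The stated 120 lies inside 113 to 125. This point does not affect it.

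**2. Effect of ignoring the strata.** With 10% drop-out, 120 × 0.9 = 108 per arm are evaluable. SE = 20 × √(2/108) = 2.72, so 8.1 / 2.72 = 2.976. Let R² be the share of CCI variance explained by the strata. The documents give no value, so it is an **assumption**, taken over 0.02 to 0.15. Under stratified allocation the true SE is 2.72 × √(1 − R²), while the unstratified test still uses 2.72.

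- True alpha = 2 × [1 − Φ(1.96 / √(1 − R²))]
- Power, unstratified test = Φ((2.976 − 1.96) / √(1 − R²))
- Power, adjusted test = Φ(2.976 / √(1 − R²) − 1.96)

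| R² (assumed) | True alpha, unstratified | Power, unstratified | Power, adjusted | Gain (points) |
|---|---|---|---|---|
| 0.02 | 0.048 | 0.848 | 0.852 | 0.5 |
| 0.05 | 0.044 | 0.851 | 0.863 | 1.1 |
| 0.10 | 0.039 | 0.858 | 0.880 | 2.2 |
| 0.15 | 0.034 | 0.865 | 0.898 | 3.3 |

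Starting from exactly 80% power (2.802 in place of 2.976):
- R² = 0.05: unstratified Φ(0.842 / √0.95) = 80.6%; adjusted Φ(2.802 / √0.95 − 1.96) = 82.0%; gain 1.4 points.
- R² = 0.15: 81.9% against 86.0%; gain about 4 points.

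Together, the loss is about 1 to 4 points for R² of 0.05 to 0.15.

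**3. Does a fully stratified rank test recover it?** Simulation: 216 patients, 10 strata, blocks of 4, normal outcome, SD 20, shift 8.1, 3,000 runs. Equal centres and a 75/25 neoadjuvant split are assumed.

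| R² | Power, plain Mann–Whitney | Power, van Elteren, 10 strata |
|---|---|---|
| 0 | 0.835 | 0.813 |
| 0.02 | 0.825 | 0.807 |
| 0.05 | 0.826 | 0.828 |
| 0.10 | 0.824 | 0.835 |
| 0.15 | 0.839 | 0.870 |

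The Monte Carlo standard error of each entry is about √(0.83 × 0.17 / 3000) = 0.007. Ten separate strata cost a little when the strata carry no information, break even near R² = 0.05, and gain above that. Steps 2 and 3 use a normal outcome; the real CCI will have many zeros, so the figures are a guide to scale.

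**4. 90-day weight.** With baseline as a covariate, the variance relative to unadjusted follow-up weight is 1 − r². The correlation r is an **assumption**; the documents give none.

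| r (assumed) | Variance remaining | Equivalent sample multiple |
|---|---|---|
| 0.5 | 75% | 1.3 |
| 0.7 | 51% | 2.0 |
| 0.8 | 36% | 2.8 |
| 0.9 | 19% | 5.3 |
| 0.95 | 10% | 10.3 |

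**The case against.** **The primary test is not wrong.** A reader might infer that the type I error is inflated or the p-values are invalid. The arithmetic shows the opposite: the error is on the safe side. This objection stands in full.

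**The power at stake is small.** A reader might set the nominal 80% against the 82% to 86% of the adjusted test and infer a gain of 2 to 6 points. That is the wrong comparison, because stratified allocation already lifts the unstratified test to 80.6% to 81.9%. R² is also assumed. A shared ERAS bundle and agreed complication definitions may limit centre effects, and operation type and fistula risk score are already listed. This stands as a limit on size.

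**The factor list may not be the full covariate set.** It follows directly on the sentence about subgroups, and its dichotomised cut-offs fit that use. So the article does not establish that the adjusted models will omit centre and neoadjuvant therapy. It establishes only that neither is among the factors named. An unshown analysis plan could add them, but the unstratified primary test is stated in the article itself.

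**Weight is an inference.** No sentence specific to weight rules out baseline adjustment; the reading rests on the general rule for numerical endpoints. That is fair, but the rule as written covers weight and provides no adjustment.

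**Prealbumin.** A reader might extend the complaint to it. The documents do not support this: it is defined as a change, so baseline is already used.

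**Conclusion.** The mismatch between stratified allocation and an unstratified primary test is in the text. It concerns efficiency and consistency, not validity. At an assumed stratum R² of 0.05 to 0.15, true alpha is about 0.044 to 0.034 and about 1 to 4 points of power are lost; at 0.02 the loss is about half a point. If the strata do not predict CCI, nothing is lost.

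The weight point concerns one secondary endpoint but is proportionally much larger. If weight is analysed under the general rule, and the baseline correlation is 0.8 to 0.95 (assumed), 64% to 90% of the variance could be removed with data the trial already collects.

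The change is worth making because it is cheap, not because the planned conclusion would otherwise be unsound.

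**What to change.** - **Primary CCI comparison:** adjust for centre and neoadjuvant therapy, with a rank-based or regression model that has both as covariates. Main effects need 4 + 1 = 5 terms rather than 10 cells. Alternatively, use a van Elteren test with small cells merged by a rule set in advance. Avoid 10 fully separate strata: 240 / 10 = 24 patients per cell is only an average, and competitive recruitment will make the cells uneven.
- **Adjusted models:** state that centre and neoadjuvant therapy enter the quantile and logistic models, and say whether the 14 listed factors are covariates, subgroups or both.
- **90-day weight:** analyse it with baseline weight as a covariate. For prealbumin, using baseline as a covariate is a minor refinement of the planned change score.

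**Cost:** a few sentences and slightly more analysis work, with no extra patients or data, fixed before any comparison by arm. If the strata are not prognostic, there is little or no gain, and a slight loss if fully separate strata are used.

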### Case report form

The following baseline patient-related parameters will be recorded:

- Age (years)- Sex- Weight (kg)- Height (m)- Body mass index (kg/m^2^)- Nutritional risk score-2002- Percent of weight loss in the 6 months prior to surgery- Charlson comorbidity index- Diabetes- Jaundice- Biliary stenting- Routine laboratory test (albumin, preabumin, bilirubin, hemoglobin, creatinine, HbA1c, CRP)- Primary disease with indication to surgical resection- ASA score- Neoadjuvant treatments

The following intraoperative parameters and events will be recorded:

- The day of operation- Type of surgical procedure (PPPD, Whipple)- Type of pancreatic anastomosis (gastric, jejunal)- The level of intraoperative contamination (clean; clean-contaminated; contaminated; dirty)- Use of epidural analgesia, TAP block, subfascial catheter- Intraoperative hypothermia (defined as body temperature < 35.5°C for more than 30 min)- Estimated blood loss (mL)- Volume of IV fluid infusion- Intraoperative blood transfusion- Fluid balance (in and out difference)- Duration of operation (minute)- Main pancreatic duct diameter- Pancreas texture (soft, intermediate, hard)- Fistula risk score

After the operation the following parameters and events will be recorded:

- Capillary blood glucose levels (every 6 h for 5 consecutive days)- Any administration of insulin (for blood glucose ≥180 mg/dL)- Occurrence of a complication (90-days)- Type of complication- The complication burden according to CCI (90-day)- The severity of complication according to Clavien-Dindo classification- The need of reoperation, reason and postoperative day- The need of unplanned intensive care treatment and the duration (days)- The day of canalization to gas and stools- The day of resumption of oral feeding- The need and duration of artificial nutrition (for the control arm)- Potential hospital discharge according to predefined criteria- The actual day of hospital discharge- Disease staging- Readmission rate (30-day)- Mortality rate (90-day)

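### The effect-modification analysis uses single cut-offs for seven continuous or scored baseline and intraoperative factors whose full values are recorded, which costs power in secondary analyses

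*Protocol article*

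**What the plan says.** The Statistical planning section of the protocol article plans quantile regression at the 25th, 50th and 75th percentiles of the Comprehensive Complication Index (CCI) "to identify factors associated with the primary endpoint and to evaluate the effect of treatment adjusting for possible residual confounding". It adds logistic regression for CCI above 23. With these same models, "the effect of PN over controls on the CCI will be also investigated within pre-specified subgroups to account for possible effect modification". The list follows directly, introduced by "The pre-specified risk factors for this analysis will be".

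Most numerical or graded entries carry one threshold. Nutritional risk screening is cut at 3 or more. The patient characteristics after it read "Body mass index (> 30)- Sex (male)- Age (>70 years)- Charlson comorbidity index (>4)- ASA score (=3". The two operative measures that come next are set as "Blood loss (≥500 mL)- Duration of surgery (>360 min". Near the end of the list stands "Fistula risk score (≥7)- ERAS overall compliance (>70". The section gives no continuous form, no reason for any threshold and no expected share of patients beyond it.

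The Case report form section collects the underlying values. The baseline items begin "Age (years)- Sex- Weight (kg)- Height (m)- Body mass index (kg/m^2^)- Nutritional risk score-2002" and go on to the Charlson index and ASA score. The intraoperative items include blood loss in mL, duration in minutes and the fistula risk score.

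The section on screening and randomization allocates patients on the evening of surgery or the next morning. The intraoperative factors therefore precede allocation and are legitimate covariates and effect modifiers. Table 2 places its randomisation visit before the intraoperative column, but the randomization section is the explicit rule.

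**The concern.** A single threshold treats patients aged 71 and 89 as alike and patients aged 70 and 71 as different. Where the effect of parenteral nutrition changes gradually with age, nutritional risk or blood loss, the two-group version captures only part of the trend, and the interaction test loses power. The sample size rests on the main effect alone, so these tests start weak. With a further loss, a null result for a given factor says very little. The same loss would apply to the search for factors associated with the CCI, if that search uses the same coding.

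Seven factors fixed before allocation are affected: nutritional risk score, BMI, age, Charlson index, blood loss, duration of surgery and fistula risk score. ASA is also graded and cut at 3, but among eligible patients it has only three levels, so less is lost. ERAS compliance is left out here because it is at least partly observed after allocation.

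**Working it through.** **The plan's own figure.** The documents give no figure for information loss. The nearest figure is 120 per group. A 30% reduction from a mean of 27 is 8.1. With SD 20, 2 × [20 × (1.96 + 0.84)/8.1]² gives 96 per arm. Dividing by the lowest Mann–Whitney efficiency, 0.864, gives 111, and adding 10% for drop-out gives 123, close to 120. This is a main-effect calculation with no allowance for interactions.

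**Information kept after one cut.** Assume a normal factor with a linear effect and a share p of patients beyond the cut c. The retained share is φ(c)²/[p(1 − p)], where φ is the standard normal density. The shares p are assumptions.

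| p | φ(c)²/[p(1 − p)] | Kept | Lost |
|---|---|---|---|
| 50% | 0.3989²/0.25 | 0.637 | 36% |
| 30% | 0.3477²/0.21 | 0.576 | 42% |
| 20% | 0.2800²/0.16 | 0.490 | 51% |
| 15% | 0.2332²/0.1275 | 0.426 | 57% |
| 10% | 0.1755²/0.09 | 0.342 | 66% |
| 5% | 0.1031²/0.0475 | 0.224 | 78% |

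**Other shapes.** These distributions are also assumed.
- Nutritional risk scores 1 to 5 (20, 30, 30, 15, 5%), cut at 3: 28% lost.
- Charlson scores 2 to 8 with 40% above 4: 32% lost.
- ASA 1 to 3 (5, 55, 40%), cut at 3: 14% lost.
- Fistula risk scores 0 to 10 with 20% at 7 or more: 45% lost.
- A skewed factor acting on its raw scale (lognormal, log SD 0.7): 58% lost at a 50/50 split and 41% at 85/15.
- A uniform factor: 25% and 62% at the same splits.

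**Interaction power.** Suppose the test has 80% power on the full scale, so its expected statistic is 1.96 + 0.84 = 2.80. After the cut, power is Φ(2.80 × √kept − 1.96).
- p = 50%: 2.80 × 0.798 − 1.96 = 0.28, power 61%.
- p = 20%: 2.80 × 0.700 − 1.96 = 0.00, power 50%.
- p = 15%: 2.80 × 0.653 − 1.96 = −0.13, power 45%.

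The interaction standard error rises by 1/√kept, which is 25% at p = 50% and 53% at p = 15%. This is a linear-model approximation.

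**Adjusted treatment effect.** If the covariates explain a share R² of outcome variance on their full scale, cutting them multiplies the standard error by √[(1 − R² × kept)/(1 − R²)].
- R² = 0.05, kept 0.637: √(0.968/0.95) = 1.01.
- R² = 0.20, kept 0.427: √(0.915/0.80) = 1.07.

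So the rise is about 1% to 7% for an assumed R² of 5–20%.

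**The case against.** The strongest reply is that the list belongs to the subgroup analysis. Its introductory phrase points most directly there, subgroups need categories, and the form of covariates in the adjusted models may be set in an analysis plan that is not shown. This stands in part. A reader might infer that the adjusted models use only the cut-offs. That is reasonable, because the subgroups are examined with the same regression models, but the article does not say so. The direct reading still leaves the defect. Categories are needed to display subgroups, not to test effect modification, and the thresholds are written into the protocol rather than left open.

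A second reply is that the percentages do not describe this trial. Normality, linearity and the split at each cut are all assumed. The planned models are quantile and logistic regression. With about 60% of patients expected to have complications, roughly 40% would score 0 on the CCI, so a normal-outcome analogy is rough. No interaction is powered. All of this stands, and the figures can only illustrate the size of the loss.

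A third reply is that at least one threshold is useful. The Discussion describes a comparable trial that enrols patients with a nutritional risk score of 3 or more, and it expects the two trials to inform the same question. This is a good reason to report that subgroup, and the proposed change keeps it.

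**Conclusion.** The point holds for the secondary analyses. The protocol fixes single cut-offs for seven factors that it records in full, and this weakens the examination of effect modification. On the reasonable but not explicit reading, it also weakens risk-factor identification and covariate adjustment. For a normal, linearly acting factor the loss is about 36% to 57% for splits from 50/50 to 85/15. It is larger at more extreme splits and smaller for short graded scores. A nominal 80% interaction power would fall to roughly 61% to 45%.

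Two stronger conclusions are tempting and not supported. One is that 36–57% is a known loss for all seven factors; the documents give no distribution for any of them. The other is that the adjusted treatment effect is compromised. Treatment is randomised, so coarse coding costs precision without causing bias. The cost is about 1–7% in the standard error under the assumed covariate strength, and the primary Mann–Whitney comparison uses none of these factors.

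**What to change.** In the Statistical planning section and its list, state that treatment-by-factor interaction will be tested with the seven factors on their recorded scale. State that the adjusted quantile and logistic models will use the same form. Fix one form per factor in advance: linear, with a log transformation for blood loss. Keep the listed cut-offs only to display subgroup results. Settle this in writing before outcome data are examined.

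No new data, visits or patients are needed. A linear or log term uses one coefficient per factor and one per interaction, the same number as a yes/no term, so the models do not grow. The cost is a shape assumption for each factor and slightly more output, because the displayed subgroups and the interaction tests are reported separately.

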According to expert opinions (7), artificial nutritional support should be implemented early postoperatively in malnourished patients, in those patients at high risk of developing malnutrition, in those who develop complications affecting oral feeding tolerance, and in well-nourished patients who do not tolerate at least 50% of their caloric and protein requirement by postoperative day 7 for any reason. Accordingly, most of the patients bearing pancreatic cancer and undergoing PD should receive some form of artificial nutritional support after the operation. Conversely, ERAS pathways promote oral food “at will” early after surgery and consider an artificial nutritional support only in selected cases (8). Furthermore, there are no convincing data on whether attaining adequate nutritional needs can be accomplished only by progressive increase of oral food intake. A study reported (9) that, the mean daily calorie and protein intake in the first 2 weeks were similar between the ERAS group and the patients managed conventionally. Anyhow, the results revealed that the total energy goal through oral feeding was not reached in both groups. Other studies did not analyze or reported incomplete data on tolerance to early postoperative oral feeding (EOF) after PD (10, 11). Robertson et al. (12) described compliance rates of 82% for resumption of oral fluids and 86% for tolerance of solid diet. Conversely, in another large study (13), postoperative oral liquids were tolerated by 55% of the patients and solid food in 53%, but compliance dropped substantially in patients with a complicated postoperative course. Thus, the available evidence suggests that using only oral feeding (food “at will”) within an ERAS protocol may be only partially adequate to achieve the nutritional needs after PD.

Given the lack of strong evidence, there is a need for a randomized clinical trial specifically designed to explore the extent to which reaching full nutritional requirements by adding parenteral feeding in the first days after surgery within an established ERAS program impacts on postoperative morbidity compared to oral food “at will” alone.

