### Pre-trial training

Before starting patient enrolment, multiple meetings will be organized to accomplish:

- Correct definition of eligibility, inclusion and exclusion criteria.- Agreement on definition of postoperative complications.- Training on randomization process and patient instruction on treatment arms.- Accordance on ERAS elements (described in Table 1).- Training of outcome assessors to record the occurrence of the primary and secondary endpoints. Each participating center will nominate two independent outcome assessors. The assessors will be trained by the single center principal investigator on the definition of complications during a dedicated pre-trial face-to-face meeting according to a modified Delphi method. In case of discordance on the assignment of the endpoint, a third expert will intervene to solve the dispute and classify the patients as complicated or not. Outcome assessors will be blinded to treatments.- Training on how to fill out correctly the case report form.

**Table 1 tab1:** ERAS items implemented in both groups.

Item	Yes	No
Preoperative counseling	X	
Prehabilitation		X
Preoperative biliary drainage		X
Preoperative stop of smoking and alcohol consumption	X	
Preoperative nutrition		X
Perioperative oral immunonutrition		X
Preoperative fasting		X
Preoperative carbohydrate loading	X	
Pre-anesthetic medication		X
Anti-thrombotic prophylaxis	X	
Antimicrobial prophylaxis and skin preparation	X	
Epidural analgesia	X	
Opioid-sparing analgesia	X	
Wound catheter and transversus abdominis plane block	X	
Minimal invasive surgery		X
Nausea and vomiting prophylaxis	X	
Avoiding hypothermia	X	
Nasogastric intubation		X
Goal-directed fluid therapy	X	
Perianastomotic drainage	X	
Somatostatin analogues		X
Postoperative multimodal analgesia	X	
Postoperative glycemic control	X	
Urinary drainage early removal	X	
Stimulation of bowel movement		X
Early and scheduled mobilization	X	
Audit	X	

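### The compliance factor (overall ERAS compliance above 70%) is partly scored after randomisation, so PN effects within compliance subgroups, or adjusted for compliance, are open to bias

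*Protocol article*

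**What the plan says.** The Statistical planning section of the protocol article plans quantile regression for the CCI (median and quartiles) and logistic regression for a CCI above 23. One stated purpose is "to evaluate the effect of treatment adjusting for possible residual confounding". With the same models, "the effect of PN over controls on the CCI will be also investigated within pre-specified subgroups to account for possible effect modification". The text continues "The pre-specified risk factors for this analysis will be" and gives fourteen factors, the last being "ERAS overall compliance (>70" per cent.

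On timing, Screening and randomization processes states: "Patients will be randomly allocated to ERAS or ERAS plus PN at 8:00 PM of the day of surgery". If the operation ends after 8 PM, allocation is at 8 AM the next morning.

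Table 1 (under Pre-trial training) has 27 ERAS rows, 17 of them marked Yes. One is "Postoperative glycemic control". Nothing in the article limits the compliance factor to items completed before allocation.

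**The concern.** A subgroup factor or covariate for a randomised treatment effect should be settled before allocation, or at least be out of reach of treatment and outcome. The listed intraoperative factors pass this test: blood loss, duration of surgery and fistula risk score are determined by the end of the operation, and PN cannot change histology. Overall ERAS compliance does not pass, because part of it is scored on the postoperative days in which PN is given and complications accrue.

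A patient who develops a complication may mobilise late or keep a urinary catheter longer, and so fall into the low-compliance group because of the outcome. If PN prevents complications, it also changes who is in each group. Within a compliance group the arms are then no longer comparable by randomisation. A finding that PN works mainly in low or in high compliers is one that readers of an ERAS trial might act on, and it could be produced by the grouping alone.

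**Working it through.** The plan gives no figure to reproduce here. The check has two parts.

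**1. Timing and weight of the postoperative items**

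- Four items marked Yes can be fulfilled only after allocation: postoperative multimodal analgesia, postoperative glycaemic control, early removal of urinary drainage, and early mobilisation. Others may extend past allocation, so four is a minimum.
- Assume equal weights on the 17 Yes items. The cut is 0.70 × 17 = 11.9, so a compliant patient meets at least 12. The other items number 17 − 4 = 13. A patient who meets 8 to 11 of those 13 is classified entirely by the four postoperative items (8 + 4 = 12; 11 + 1 = 12).
- If all 27 rows were scored, the cut would be 0.70 × 27 = 18.9, so 19. The same four items would decide for anyone meeting 15 to 18 of the other 23.

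**2. Illustrative simulation**

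Inputs from Statistical planning: 60% of patients complicated; CCI in complicated patients with mean 27 and SD 20 (drawn from a gamma distribution); a true PN effect of zero or a 30% reduction. The planned difference over all patients is then 0.60 × 27 × 0.30 = 4.86 points.

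Assumed inputs, because the document has none: compliance with mean 80% and SD 10 percentage points, cut at 70%; PN shifts it by the amount shown; each 27 CCI points shifts it by 0 or −6 percentage points. There are 400,000 patients per row. Effects are differences in mean CCI, PN minus control; the OR is for a CCI above 23.

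| True effect | PN shift | Complication shift | Unadjusted | Adjusted | High / low compliers | Adjusted OR |
|---|---|---|---|---|---|---|
| none | 0 | 0 | 0.06 | 0.06 | 0.07 / 0.00 | 1.01 |
| none | 0 | −6 | −0.04 | −0.06 | −0.09 / 0.01 | 0.99 |
| none | −5 | 0 | −0.07 | −0.07 | −0.06 / −0.10 | 0.99 |
| none | −5 | −6 | −0.07 | −2.44 | −1.55 / −4.11 | 0.78 |
| none | +5 | −6 | −0.02 | 2.13 | 1.39 / 5.16 | 1.24 |
| none | −10 | −6 | −0.11 | −4.72 | −3.02 / −6.93 | 0.62 |
| 30% | 0 | 0 | −4.82 | −4.82 | −4.80 / −4.93 | 0.55 |
| 30% | 0 | −6 | −4.81 | −4.34 | −2.55 / −9.59 | 0.55 |
| 30% | −5 | −6 | −4.81 | −6.16 | −3.41 / −11.67 | 0.44 |
| 30% | +5 | −6 | −4.78 | −2.63 | −1.86 / −6.34 | 0.67 |
| 30% | −10 | −6 | −4.72 | −8.03 | −4.31 / −13.22 | 0.35 |

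What follows:

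- With no PN effect, one path alone causes no bias. Bias needs both PN and complications to act on compliance, and its sign follows the sign of the PN shift.
- With a true reduction, the complication path alone separates the subgroups. The adjusted mean moves only from −4.81 to −4.34, and the OR from 0.54 to 0.55. On medians, which the plan models, the difference is −2.82 overall but −0.23 in high and −9.06 in low compliers.
- Part of the gap in points arises because low compliers have a higher CCI (control means about 27 against 12 when this scenario is rerun). It does not vanish on the relative scale: 2.55/12 = 21% against 9.59/27 = 36%, where the truth is 30% for everyone.
- The gap shrinks with a weaker complication path. Rerun with shifts of −3 and −1.5 points, the high/low effects are −3.9/−8.1 and −4.4/−6.6.

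**The case against.** **The path from PN to compliance is inferred.** Procedures common to both arms prescribes insulin for raised glucose in either arm. If the glycaemic item is scored as that care having been given, a hyperglycaemic PN patient who receives it is compliant. That hyperglycaemia is a secondary outcome does not show that PN lowers compliance. This stands, and so the direct path is only possible.

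**The shifts of 5 and 10 points are large for one item.** Losing 30 percentage points of attainment on one of 17 items lowers overall compliance by 30/17 = 1.8 points. With that shift, no PN effect and the same complication path, the adjusted estimate is about −0.8 to −0.9 points. The standard error of a mean difference with 108 evaluable patients per arm is about 2.8 (20.4 × √(2/108)). This stands too.

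**The Introduction's evidence is narrower than it looks.** The statement that "compliance dropped substantially in patients with a complicated postoperative course" concerns tolerance of oral liquids and solid food in one cited study, and oral feeding is not a row of Table 1. It makes a link from complications to compliance plausible but does not document it for the scored items.

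**Use as a covariate is not explicit.** The list directly follows the subgroup sentence, so its nearest reading is a list of subgroup factors. Use for adjustment follows from the shared models, one step less plainly.

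**An article may leave the scoring of compliance to a fuller document.** That is fair, and the absent scoring rule is not the point. The point is the word overall in a fixed list: on its plain meaning it takes in the postoperative items.

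None of this removes the structural problem. If PN works as H1 states and complications lower postoperative compliance, the subgroup effects are distorted without any direct PN path.

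**Conclusion.** The point holds as a structural weakness in supplementary analyses. Following the plan as written conditions the PN effect on a variable that is partly determined after randomisation. The compliance-subgroup effects, and the compliance-adjusted effects if the factor enters the models as a covariate, are open to bias and artificial interaction. The first is explicit in the plan; the second is its natural reading.

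Two stronger conclusions might be inferred and are not supported. One is that these effects are certainly biased, by a known amount or in a known direction. The document gives no compliance data, the PN path is inferred, and under no PN effect a single path produces no bias; the simulated figures only show what could happen under stated assumptions. The other is that the main result is compromised. The primary Mann-Whitney comparison does not use compliance and is not affected. Nor does the criticism extend to the listed intraoperative factors, which precede allocation.

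**What to change.** Define the compliance factor for the treatment-effect models and subgroups from ERAS items completed before randomisation only, and name those items. Alternatively, remove it from the models and the subgroup list. In either case report overall and postoperative compliance by arm as a descriptive process measure. Settle this before any analysis by arm.

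The cost is the redefinition of one variable; the sample size and primary analysis stay as they are. One check is needed: the article's Case report form section shows no compliance field and no field for some preoperative items, such as counselling and carbohydrate loading, so the team should confirm that item-level data are captured. Any compliance score, including the present one, needs them.

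The downside is that a pre-randomisation score covers fewer items and no longer answers whether the PN effect differs by adherence to the full pathway.
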